## **3. Proposed study**

### **3.1 Study design**

We propose a non-inferiority randomized trial. The girls who received 2 doses of Gardasil® 5 years ago (see study population section) will be randomly assigned to a «2-dose» group where they will not receive additional doses of vaccines, or to a «3-dose» group where they will receive a 3rd dose of vaccine. The girls and their parents will know the group to which they were assigned. Blood samples will be collected among a subgroup of girls (250 in each of the two groups) in order to determine antibody titers (objectives 2.2.a and c). The persons assessing the primary and secondary outcomes (HPV and antibody testing) and the data analysts (statisticians) will be blinded to group allocation.

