### **3.3 Enrolment**

After approval by the Commission d'Accès à l'Information we will contact the Quebec health insurance board (Régie de l'Assurance Maladie du Québec, RAMQ) in order to obtain the contact information of girls aged 9 years on September 30th, 2008 (i.e. born between October 1st, 1998 and September 30th, 1999 for the first enrolment year), 9 years on September 30th, 2009 (i.e. born between October 1st, 1999 and September 30th, 2000 for the second enrolment year), 9 years on September 30th, 2010 (i.e. born between October 1st, 2000 and September 30th, 2001 for the third enrolment year), 9 years on September 30th, 2011 (i.e. born between October 1st, 2001 and September 30th, 2002 for the fourth enrolment year).

From September 2013 to June 2014 we will contact the girls' parents by mail to invite those who received 2 doses of Gardasil® during the 2008-2009 academic year. The letter will explain the purpose of the project, how it will be carried out and details on inclusion criteria. This same step will be carried out in 2014, 2015 and 2016.

A phone number and an e-mail address will enable parents to contact a research nurse (1) to obtain further information, (2) to check eligibility and (3) to take an appointment with a research nurse at the coordinating center.

During this appointment, the research nurse will confirm the participant's eligibility, will obtain informed consent from the girl and her parent, will perform a urine pregnancy test on the girl and will randomize her to one of the groups, administer the 3rd dose if she was assigned to the «3rd dose» group and collect the blood sample if she is part of the subgroup targeted by the secondary objective on immunogenicity. A financial compensation will be offered to the girl and parent 20,00\$ each) for this face-to-face appointment. The participant will collect the first HPV vaginal sample after receiving explanations on the self-sampling procedure and will fill the first questionnaire. A financial compensation will be provided for each self-sampling kit received (5,00\$ per sampling, then 10,00\$ per sampling when the girl turns 18 years of age).

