### **3.4 Conduct of the study**

After the first visit, the girls will have to perform vaginal self-samplings every 6 months and fill an online questionnaire once a year. They will receive an e-mail or a text message (SMS) 2 weeks before the target date. The self-sampling kits will be sent by mail. A reminder (e-mail or SMS) will be sent if the tube is not returned or the questionnaire not filled 2 weeks after the target date. A

second reminder (e-mail, SMS or phone call) will be made 2 weeks later (i.e. 1 month after the target date).

The 500 girls included in the immunogenicity aspect of the study will be seen at the coordinating center 90 and 120 months after the first injection, in order to collect blood samples which will be used to measure presence and titers of antibodies against HPV. Because there were less losses to follow-up than expected, and in order to reduce the costs as much as possible while being able to meet the secondary objective on immunogenicity, the blood sampling at month 90 will be performed in only 350 participants (175 per group). Section 3.8.2 specifies the number of participants required at the end of the study to reach the statistical power needed for this objective.

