### 3.6 Randomization

Randomization will be performed via a web service. It will be stratified by centre (Montréal, Saguenay-Lac-St-Jean and Quebec City). Blocks varying in size between 4 and 8 participants will be used within each stratum.

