### 3.7 Bias protection

We have chosen not to administer placebo to the girls randomized to the «2 dose» group for many reasons.

First, given that it is primarily an evaluation of the vaccination program, we want to perform an evaluation as close as possible to the real world environment. The girls will know if they received 2 or 3 doses whether or not the 3rd dose at 60 months is offered as part of the Quebec program. The only way through which knowledge of the number of doses received can influence the primary outcome is if it modifies the sexual behavior. Some people were worried about the fact that vaccination against STI could lead to more risky sexual behaviour, resulting from a false sense of security. Fortunately, the data available today do not support this hypothesis(79–81).

The main outcome is the detection of a virus in cervical secretions; it is therefore quite unlikely that the knowledge of the study group can influence that in anyway. The professionals in charge of the laboratory tests will not have access to the participants' randomization group. Similarly, the persons that will analyze potential screenings test will not know the group to which the participants were assigned.

Taking into consideration the related costs, risks, and inconvenience (discomfort, side effects associated to injecting a placebo) and its very low utility in improving the validity of the study results; it did not seem ethical or useful to us to include a placebo for the control group. The primary outcome will be measurement of persistent infections and completion of annual questionnaires enabling us to control for sexual behaviors in the analysis.

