### 3.9 Analysis

Descriptive analyses will be used to describe the participants and compare the two study groups. Specifically, the following analyses will be performed for each of the objectives mentioned in section 2.

For the primary objective:

A survival analysis (time to event analysis) will be performed in order to answer the main study questions. This approach will take into consideration the different duration of follow-up resulting from the fact that the date of entry in the cohort will vary between participants. Time 0 will be defined as the date of randomization. The time of event will be defined as the first occurrence of a persistent infection. Participants with no persistent infection will be censored (right-censored) at: (a) loss to follow-up, (b) death or (c) end of the study whichever comes first. The preliminary analyses will include the comparison of the Kaplan-Meier curves using a non-parametric test (*log-rank test*, *Wilcoxon*) describing how the proportion of participants developing a persistent infection varies over time in each group. The main non-inferiority analysis will rely on the Hazard ratio's (HR) 95% confidence interval. Adjusted analyses will take into consideration the potential confounding factors collected with the annual questionnaire. If the HR's upper limit is not higher than 1.05 (representing a 5% difference of efficacy between the two schedules), we will conclude to a non-inferiority of the 2-dose calendar.

This analysis will then be repeated with the « intention-to-treat » method to evaluate the differences generated by a change in the exposure's definition. Sensitivity analyses will also be performed to evaluate the impact of modifying the outcome's definition. Indeed, it is likely that some girls will not exactly respect the vaginal self-samplings' schedule. We will vary the primary outcome's definition (e.g. consider as persistent infection only if the sample were consecutive and 6 months apart, or

consider as persistent infection a situation where the same type of virus was identified in two consecutive samples regardless of the number of months between the samples).

For the secondary objectives on immunogenicity (objectives 2.2.a and c), two analyses will be performed to measure non-inferiority at month 120:

1) An intention-to-treat analysis (*ITT analysis*) in which all the serologic results available will be included.

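### The plan adjusts for sexual behaviour reported after open allocation and does not say whether the 1.05 rule uses the adjusted or the unadjusted hazard ratio

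*Protocol*

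**What the plan says.** Section 3.9 rests the main non-inferiority analysis on the 95% confidence interval of the HR. It continues: "Adjusted analyses will take into consideration the potential confounding factors collected with the annual questionnaire". The next sentence gives the decision rule, an upper limit of the HR not above 1.05, without saying whether that HR is adjusted. No covariates are listed and no time of measurement is set.

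Section 3.7 says which variables are meant. It counts among the trial's protections the "completion of annual questionnaires enabling us to control for sexual behaviors in the analysis".

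On timing, section 3.4 states: "After the first visit, the girls will have to perform vaginal self-samplings every 6 months and fill an online questionnaire once a year". Section 3.3 adds that at the enrolment visit the participant "will fill the first questionnaire", and mentions this after randomisation and the third dose. On masking, section 3.1 states: "The girls and their parents will know the group to which they were assigned".

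Section 3.7 also describes how an open design could affect the result: "The only way through which knowledge of the number of doses received can influence the primary outcome is if it modifies the sexual behavior". It then discounts that route: "Fortunately, the data available today do not support this hypothesis".

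**The concern.** A confounder of a randomised comparison has to precede allocation. Behaviour reported one or more years after an open allocation does not. If knowing the number of doses changes behaviour, behaviour lies on the path from assigned schedule to persistent infection, and conditioning on it removes that part of the effect. If girls in the two arms only report behaviour differently, adjustment brings the reporting difference into the HR.

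This also conflicts with the stated purpose. Section 3.7 omits a placebo because the trial is to resemble the programme, in which girls know how many doses they have had. That question includes any behavioural response, which a behaviour-adjusted HR would take out.

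The wording of the rule compounds the problem. Two analysts following section 3.9 could apply 1.05 to different estimates and each claim to follow the protocol. With few events and no covariate list, those estimates could differ.

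**Working it through.** **1. Side-by-side reading.** Adjustment variables: potential confounders from the annual questionnaire (3.9), namely sexual behaviours (3.7). Timing: yearly after the first visit (3.4), with a first questionnaire at that visit whose order relative to allocation is not fixed (3.3). Masking: participants know their group (3.1). Causal path: knowledge of allocation → sexual behaviour → outcome (3.7). Together these make follow-up behaviour a possible mediator that the plan labels a confounder.

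**2. Expected events, reproducing the plan's figure.** Inputs from section 3.8.1 and Table 3, 5-year row: effective size 1431 per group, cumulative incidence 15.02%, efficacy 95% (3 doses) and 94% (2 doses).
- 3-dose group: 1431 × 0.1502 × 0.05 = 10.7
- 2-dose group: 1431 × 0.1502 × 0.06 = 12.9
- Total: 1431 × 0.1502 × 0.11 = 23.6, against 23 stated in section 3.8.1
- Recruitment: 1431 / (0.99 × 0.98 × 0.97 × 0.96 × 0.95) = 1667.3, against 1667 stated

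Both figures reproduce.

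**3. Events per model parameter at 23 events.**
- Treatment plus 2 covariates: 23/3 = 7.7
- Treatment plus 3 covariates: 23/4 = 5.8
- Treatment plus 8 covariates: 23/9 = 2.6

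The protocol gives no number of covariates; these cases are examples. They show sensitivity to model choice, which baseline covariates would share. They do not measure bias.

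**4. Illustration of the change in estimand.** None of these inputs is in the documents. Assume no biological difference between schedules, a share p₃ = 0.50 of 3-dose girls in a higher-risk behaviour category, a share p₂ of 2-dose girls in it, and risk ratio r for that category. With rare events the total-effect HR is approximately

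(p₂·r + 1 − p₂) / (p₃·r + 1 − p₃)

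and the HR conditional on behaviour is 1.00.

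| r | p₂ | Total-effect HR | Adjusted HR |
|---|---|---|---|
| 2 | 0.48 | 1.48/1.50 = 0.99 | 1.00 |
| 5 | 0.40 | 2.60/3.00 = 0.87 | 1.00 |
| 2 | 0.52 | 1.52/1.50 = 1.01 | 1.00 |
| 5 | 0.60 | 3.40/3.00 = 1.13 | 1.00 |
| any | 0.50 | 1.00 | 1.00 |

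The total-effect HR passes 1.05 once the 2-dose share is higher by more than 0.05 × 1.5 / 1 = 7.5 percentage points (r = 2) or 0.05 × 3 / 4 = 3.75 points (r = 5). In those cases adjustment would hide a disadvantage that the programme would experience. The last row shows that mediation has no effect when behaviour does not differ by arm.

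At 23 events the standard error of the log HR is about √(4/23) = 0.42, larger than any of these shifts. The table therefore shows a change in what is estimated. It does not predict how the decision would fall.

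**The case against.** The strongest reply is that section 3.9 names the HR confidence interval as the main analysis and mentions adjusted analyses separately, and that the sizing in section 3.8.1 rests on a log-rank test without covariates. That fits an unadjusted decisive HR. This stands. A reader might infer that the decision rests on the adjusted HR and so loses its randomised interpretation, but the protocol does not say so. It only leaves the choice open.

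Second, the first questionnaire is filled at the enrolment visit, so the covariates need not all postdate allocation. This also stands, but no sentence restricts adjustment to that questionnaire, and section 3.3 does not place it clearly before allocation.

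Third, section 3.7 regards a behavioural shift as unsupported by data. If that is right, mediation does no harm. Confounding does not then justify adjusting for follow-up behaviour in the randomised comparison either.

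Fourth, the primary set is per protocol (section 3.5.1) and excludes girls who take an off-protocol dose. If seeking such a dose is related to behaviour, some adjustment is defensible. That supports pre-allocation factors. It does not support conditioning without restriction on a variable that allocation may have changed, and the protocol expects few such exclusions.

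Fifth, 23 events is near the low end of the 22 to 52 in section 3.8.4, and a minimum number of events per covariate is only a rule of thumb. Both points are accepted, and no cap on covariates follows from the documents.

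A reader might also infer that the analysis leaves out centre, since randomisation is stratified ("It will be stratified by centre", section 3.6) and section 3.9 does not mention it. That would be reading an omission into silence. Strata are commonly specified in the statistical analysis plan, which is not at hand.

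**Conclusion.** The point holds in limited form. The protocol states, and does not merely leave open, that sexual behaviour from annual questionnaires will be adjusted for as confounding. It does not limit this to values fixed before allocation, and it attaches the 1.05 rule to an unidentified HR. Adjusting for follow-up behaviour can change the estimand or add reporting bias if behaviour or its reporting differs by arm. The direction cannot be known in advance. The documents give no basis for its size; under the assumed inputs above, the total-effect and adjusted HRs differ by up to 0.13 in either direction, and by nothing if behaviour does not differ. Separately, about 23 expected events make the HR sensitive to which covariates are chosen. It is not shown that the decisive HR is the adjusted one, nor that centre is left out.

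**What to change.** State in section 3.9, or in the statistical analysis plan with a cross-reference, that the non-inferiority decision uses one pre-specified HR. It should be unadjusted or adjusted only for listed factors fixed before allocation, and preferably stratified by randomisation centre. First-questionnaire items qualify only if that questionnaire is completed before the allocation is revealed, so section 3.3 should state the order actually followed. Report follow-up sexual behaviour by arm descriptively and use it only in models labelled exploratory. Amend section 3.7 to match. The cost is a few sentences, with no new data and no change in sample size, provided this is settled before the analysts see results by arm.

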### 3.8 Sample size and feasibility of enrolment and follow-up.

#### 3.8.1 Sample size needed to answer the primary research question.

The sample size was calculated to test the primary hypothesis of non-inferiority of a schedule with 2 doses administered 6 months apart, compared to a 3-dose schedule (0, 6, 60 months). We fixed the power at 90% as recommended for non-inferiority trials(63). The calculations were based on a bilateral log rank test with alpha set at 0.05 (corresponding to an alpha of 0.025 for a unilateral non-inferiority test) which is close to a test based on a 95% confidence interval derived from a Cox model. The non-inferiority margin will be fixed at 5%. Based on the data available in multicentric clinical trials measuring the efficacy of a schedule with 3 closely administered doses, the cumulative incidence of persistent infections was assumed to vary from 10% to 20%(23,82) during a 5-year period and the efficacy of the 2-dose schedule is expected to vary from 91 to 95%(21,30,83). The long term efficacy of the 3-dose schedule is unknown but was evaluated at 95%, which corresponds to an annual cumulative incidence of persistent infections of 0.5 to 1% among vaccinated girls (Table 1). The 2-dose schedule could therefore be declared non-inferior if we observed a cumulative incidence of persistent infections of 1 to 2%. Table 1 summarizes the various scenarios that were evaluated to calculate the sample size.

In other words, if we agree to lose a maximum of 5% of the vaccine efficacy (VE) with a 2-dose schedule, in order to conclude that it is non-inferior, we would agree to have a  $VE \geq 90\%$  for the 2-dose schedule. Therefore with a rate of 10%, 15% and 20% of persistent infections in the absence

of vaccination, we estimate to respectively observe a rate of 0.5%, 0.75% and 1% of persistent infections in the group vaccinated with 3 doses and a non-inferiority accepting a maximum of 5, 8 and 10 persistent infections per 1000 participant among the group vaccinated with 2 doses.

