In other words, when considering the cumulative incidence of persistent infections per age and the revised percentage of losses to follow up, for a 95% efficacy in the 3-dose group, a 94% efficacy in the 2-dose group and the enrolment of 2420 girls per group with a 4-year follow up, we will have 23 persistent infections, the same number of persistent infections that could be achieved by recruiting 1667 girls per group with a 5-year follow up or 1372 girls with a 6-year follow up.

We will therefore try to recruit 3334 (1667 X 2) participants and maintain a 5-year follow up for all of them. If this objective could not be achieved even with an additional year of enrolment, we will consider an additional follow-up of 6 months or 1 year depending on the number recruited.

Update, August 20, 2018: we recruited and randomised 3364 participants. Recruitment completed.

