## **5. Ethics considerations**

There are specific ethical challenges related to the enrolment of minors. However, the enrolment of minor is essential to meet our primary research question. Girls aged 18 years or more are (1) not targeted by the vaccination program(20); (2) they do not have the same response to the vaccine as younger girls(25,26) and (3) on average, they have a sexual experience that is very different from younger teenagers(92). Our team has vast experience in the enrolment and retention of this type of participant(91,93–95). We will first contact the girls' parents and they will decide to present the project to their child or not. Then a member of the team (nurse) will make sure to obtain both the parents' and the girls' consent. Randomization is explained by the state of «clinical equilibrium» on the primary research question. The risks associated with the intervention are well known by the girls and their parents given that they have already received two doses of Gardasil®. These are mainly local side effects as redness and pain at the injection site(20).

Given the immunogenicity and efficacy data which are available, the primary research hypothesis is that a schedule with 2 doses administered at a 6 month interval is non-inferior to a 3-dose schedule (0, 6, 60 months). If on the contrary, the non-inferiority of the 2-dose schedule could not be demonstrated, the girls in the 2-dose group will be offered a 3rd dose free of charge at the end of the study or at any other time fixed by the research team and the monitoring committee.

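### The primary non-inferiority limit of HR 1.05 (section 3.9) does not match the 95%-to-90% efficacy tolerance in section 3.8.1, which at the assumed 3-dose efficacy of 95% is an HR of 2.0

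*Protocol*

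**What the plan says.** Section 3.8.1 says "The non-inferiority margin will be fixed at 5" per cent and explains the figure in terms of efficacy: "if we agree to lose a maximum of 5% of the vaccine efficacy (VE) with a 2-dose schedule", the 2-dose VE must still be at least 90%. It also gives rates: 0.5 to 1% with three doses, and up to 1 to 2% still acceptable with two. Every row of Table 1 carries the same definition, 95% to 90%. The planned power is 90%, with a "bilateral log rank test with alpha set at 0.05 (corresponding to an alpha of 0.025 for a unilateral non-inferiority test").

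The January 2016 revision keeps these hypotheses, "for a 95% efficacy in the 3-dose group, a 94% efficacy in the 2-dose group", and expects 23 persistent infections from 1667 girls per group followed for 5 years. Section 3.8.4 gives a range of 22 to 52.

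Section 3.9 bases the main analysis on the 95% confidence interval of the hazard ratio: "If the HR's upper limit is not higher than 1.05 (representing a 5% difference of efficacy between the two schedules"), non-inferiority is concluded. Section 5 attaches a consequence for the whole 2-dose group: "If on the contrary, the non-inferiority of the 2-dose schedule could not be demonstrated", those girls are to be offered a further dose.

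**The concern.** The figure of 5% appears on two scales. In section 3.8.1 it is an absolute loss of five points of vaccine efficacy against unvaccinated girls. In section 3.9 it has become a 5% relative increase in hazard between two vaccinated groups, and the parenthesis there treats the two as the same. They are far apart when efficacy is high, because the rate left after vaccination is small and five VE points doubles it.

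This threshold alone decides the primary objective, and section 5 ties an action to missing it. If 1.05 stands, the trial is very likely to miss it even when the two schedules protect equally well.

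**Working it through.** **Inputs.** 3-dose VE 95%, lowest acceptable 2-dose VE 90%, one-sided alpha 0.025, power 90% (section 3.8.1). Planning alternative 95% v 94%, and 23 events (January 2016 revision). 15.02% cumulative incidence without vaccination at 5 years and an effective 1431 per group (Tables 2 and 3). 22 to 52 events (section 3.8.4). HR limit 1.05 (section 3.9).

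**1. The plan's own figures.**
- Events: 1431 × 0.1502 × (0.05 + 0.06) = 23.6, which matches the stated 23.
- Table 1, 15% baseline, 95% v 94%: the printed 1431 per group is reproduced by Freedman's log-rank formula with the 90% VE limit, if the printed rates are read as annual over 5 years. The ratio of hazards at the limit and at 94% is r = ln(1 − 0.015)/ln(1 − 0.009) = 1.672. Events = (1.960 + 1.282)² × ((1 + r)/(1 − r))² = 166. The 5-year risks are 1 − 0.991⁵ = 0.0442 and 1 − 0.985⁵ = 0.0728. So n = 166.2/(0.0442 + 0.0728) = 1421. All 15 cells come within 3% in this way.
- Table 1 is therefore built on the 90% VE limit. A limit of 1.05 would give over a million per group at a true HR of 1.0 for a 15% baseline, and no solution at 1.2.

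**2. Converting between the scales.** VE = 1 − relative risk, so HR ≈ (1 − VE of 2 doses)/(1 − VE of 3 doses).
- Tolerance 95% to 90%: 0.10/0.05 = 2.0.
- Planning alternative 95% v 94%: 0.06/0.05 = 1.2.
- HR 1.05 turned back into efficacy: 1 − 0.05 × 1.05 = 94.75%, a loss of 0.25 points, one twentieth of the stated tolerance.

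**3. Chance of declaring non-inferiority.** With E events and 1:1 allocation, SE(ln HR) ≈ 2/√E. The chance is Φ(ln(limit/true HR)/SE − 1.96). For E = 23, SE = 0.417, and the observed HR must not exceed 1.05 × exp(−1.96 × 0.417) = 0.46.

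| Events | Limit 1.05, HR 1.0 | Limit 1.05, HR 1.2 | Limit 2.0, HR 1.0 | Limit 2.0, HR 1.2 |
|---|---|---|---|---|
| 23 | 3.3% | 1.1% | 38% | 23% |
| 52 | 3.7% | 0.7% | 71% | 45% |
| about 116 | 4.5% | 0.4% | 96% | 79% |

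The 116 events follow from 1431 per group with Table 1 rates read as annual over 5 years: 1431 × (0.0369 + 0.0442). An exact conditional test with 23 events needs at most 6 in the 2-dose group to meet 1.05. The chance of that is 1.7% at HR 1.0 and 0.5% at HR 1.2.

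**4. Events for 90% power.** E = 4 × (1.960 + 1.282)²/ln(limit/true HR)².
- Limit 1.05, true HR 1.0: 17,656 events, or 17,656/(2 × 0.1502 × 0.05) ≈ 1.18 million girls per group.
- Limit 1.05, true HR 1.2: no solution, because 1.2 lies beyond the limit.
- Limit 2.0: 88 events at HR 1.0 and 162 at HR 1.2.

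**The case against.** **Is 1.05 a deliberately stricter limit?** Section 3.9 does not present it so. It says that 1.05 represents the 5% efficacy difference, and the sample size rests on 95% to 90%. A statistical analysis plan with another limit would conflict with the protocol sentence and would not correct it.

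**Is 2.0 the only limit section 3.8.1 supports?** Not without conditions, and this part of the objection stands. The value 2.0 holds only if 3-dose VE is 95%, and the section says the long-term figure is unknown. A five-point loss would be 0.07/0.02 = 3.5 at a 3-dose VE of 98% and 0.15/0.10 = 1.5 at 90%. The section also gives maxima of 5, 8 and 10 infections per 1000 in the 2-dose group. Read literally, those are about the assumed 3-dose rates. They agree with 95% to 90% only as an excess over the 3-dose group (0.05 × 10%, 15% and 20%).

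**Stronger readings that the documents do not support.**
- A reader might infer that the trial must fail whatever the truth. It could pass if two doses were truly much better than three, since an observed HR of 0.46 or less would do with 23 events.
- A reader might infer that the rule classes the planning scenario as inferior. An HR of 1.2 lies inside the null region of the non-inferiority test. The trial would fail to show non-inferiority, which is not a demonstration of inferiority.
- A reader might infer that a limit of 2.0 restores 90% power. With 22 to 52 events it does not.

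**Conclusion.** The concern holds. The limit in section 3.9 and the tolerance in section 3.8.1 and Table 1 cannot both be meant, and nothing in the protocol reconciles them. On the protocol's own numbers the parenthesis in section 3.9 is wrong by a factor of twenty in VE points (0.25 against 5).

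Under the 1.05 rule the chance of declaring non-inferiority is below 5% at true HRs of 1.0 and 1.2 for each event count examined (23, 52 and about 116). This finding does not depend on which count is right. The power under a limit of 2.0 does: at HR 1.2 it runs from 23% with 23 events to 79% with about 116.

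The calculations assume proportional hazards, 1:1 allocation, the usual large-sample variance of ln HR, and a 3-dose VE of 95%. The point must be fixed, because this threshold decides the primary objective and feeds the action in section 5.

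**What to change.** Before any unblinded comparison:

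- In section 3.9, replace 1.05 and its parenthesis by the limit that the protocol's own definition implies, 2.0 = (1 − 0.90)/(1 − 0.95). State that it rests on a 3-dose VE of 95%, and have the sponsor confirm it. Use the same limit in section 3.8.1 and for objective 2.2.b.
- Reword the sentence on 5, 8 and 10 infections per 1000 as an excess over the 3-dose group, or otherwise reconcile it with 95% to 90%.
- Restate the power under the corrected limit: about 38% (HR 1.0) and 23% (HR 1.2) with 23 events, and 71% and 45% with 52. About 88 and 162 events are needed for 90%.
- Record that the change follows the definition already in section 3.8.1. State whether the interim analysis planned for 2018 (section 4.3) had shown comparative data, since moving from 1.05 to 2.0 will otherwise look like a loosening after the fact.
- As support, report the difference in Kaplan-Meier cumulative incidence at 5 years from randomization, which is about 10 years after the first dose. Give its 95% CI and set it against about 7.5 per 1000 (0.05 × 15.02%).
- Reconcile sections 3.8.1, 3.9 and 5, so that the action in section 5 depends on a single stated criterion.

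The text change is small and needs no extra participants or procedures. The low expected event count is a separate limit on power, and this amendment does not remove it.
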